### Best Practice Alert

When a patient meets the eligibility criteria, a best practice alert (BPA), displayed in Figure 2, will be triggered in Epic, RMG’s electronic health records (EHR) system. The BPA pop-up screen provides instructions for referring a patient to Project YES, including a brief overview of Project YES, its potential benefits, and how to access it. If the patient indicates that they are interested, the provider can offer SSI in 1 of 2 ways:

Send the patient a QR code or a link to participate in the SSI through MyChart (the patient front-end of Epic). The MyChart message will include a link to Project YES at the Lab for Scalable Mental Health website and instructions for participating.Provide the patient with a QR code displayed in the BPA that patients may scan using their mobile device, allowing for the retrieval of Project YES for later use. The QR code is also included in the after-visit summary for later use. The QR code will direct patients to Project YES at the Lab for Scalable Mental Health website.

**Figure 2 figure2:**
[figure not shown]
Best practice alert screen.

### Educating Providers on Project YES

First, to ensure representation from participating departments, the implementation team included a pediatrician from the pediatrics department and a pediatric clinical psychologist and pediatric psychiatrist from the behavioral health department. Initial permission and buy-in were sought from the key leadership, including the chief of pediatrics and chief of behavioral health, before designing the workflow. The SSI workflow is targeted toward pediatric and behavioral health providers, including pediatricians, nurse practitioners, clinical psychologists, and master’s-level mental health clinicians. All pediatric medical providers and integrated behavioral health providers will be given a brief presentation by members of the implementation team at monthly department meetings, 4 weeks before launching the workflow, and again the week before launch. The introductory presentation covers the gap in care that SSIs can fill, the core elements of Project YES and its 3 interventions, an example of 1 of the SSIs, the evidence base for Project YES, and instructions for referring patients to Project YES during care. Monthly check-ins at department meetings will be held to review processes, answer questions, and gather assessments as well as informal feedback. The monthly check-ins are led by the pediatric behavioral health lead, who is available to answer any questions and address and track comments or concerns. Her contact information is also provided on all materials in the event a provider has questions in real-time.

Each unique clinic also holds individual site meetings where the behavioral health lead will reiterate the core components of Project YES to the staff and providers at each individual clinic. This will also provide the lead an opportunity to introduce new clinical team members to the intervention and referral processes during their orientation. To allow for broader dissemination of information, a monthly behavioral health newsletter sent to all staff in behavioral health and pediatrics will also contain information about the intervention. Lastly, additional materials, such as the PowerPoint slides and other informational materials, will be posted to department shared drives for on-demand review.

### Patient Participation

Patients will receive an invitation to participate with a link to the SSI and instructions for participating through MyChart (Multimedia Appendix 1). The patient will click on the link in their MyChart messages that will take them to the Lab for Scalable Mental Health’s website. They will be asked to select the module they want to participate in and indicate that they are aged between 13 and 17 years and a patient at RMG in Massachusetts before beginning. The patient will not enter any potentially identifying information. By entering that they are an RMG patient, the Lab for Scalable Mental Health will be able to filter RMG’s data for the program evaluation. Before and after completing the module, the patient will be invited to complete a series of anonymous, optional questionnaires within Project YES’ Qualtrics interface. In the event a participant in Project YES experiences distress, the Project YES platform provides a “Need help now?” button on the main website and on each page of the platform that leads to [28]. The linked page provides immediately accessible crisis resources such as the Crisis Text Line, the National Suicide Prevention Lifeline, and a Hotline for LGBTQ+ Youth.

### Data Collection

Provider referral records will be collected through RMG’s EHR, and anonymous patient engagement and outcomes data will be collected within Project YES’ Qualtrics interface by the Lab for Scalable Mental Health and sent to RMG for analysis. Table 1 describes the specific data to be collected and the corresponding methods of analysis.

**Table 1 table1:** Overview of data collected and analytic methods.

Data	Items	Analytic methods	
Behavioral health and primary care providers: EHR^a^ data	Number of eligible patients seen. Number of referrals made. Reasons indicated for not providing SSI^b^ (patient inappropriate, not interested, or other). Number of patients selecting QR code versus MyChart message access.	Descriptive statistics: proportion of providers in each department offering SSI.	
Patients: engagement metrics and feedback	Number of RMG^c^ patients who entered the site. Total number of patients who completed the SSI. Program Feedback Scale		Descriptive statistics.
Providers: data collected at monthly behavioral health and pediatric department meetings	Acceptability of Implementation Measure (AIM). Feasibility of Implementation Measure (FIM). Intervention Appropriateness Measure (IAM).	Descriptive statistics. Repeated measures ANOVA.	

^a^EHR: electronic health record.

^b^SSI: single-session intervention.

^c^RMG: Reliant Medical Group.

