## Results

The program was initiated in November 2022 at 1 site to ensure Epic components functioned as intended and then expanded across all sites in December 2022. The program will continue for 6 months before the program evaluation will commence; however, referral, implementation assessment, and patient engagement data will be reviewed iteratively to identify any adaptations that need to be made. Data analysis and manuscript writing are expected in the summer of 2023.

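### Repeated measures ANOVA on ratings taken at monthly meetings drops any provider with one missing rating; a mixed model would keep them in the test of change

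*Protocol article*

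**What the plan says.** In the Data Collection section, Table 1 has a row labelled "Providers: data collected at monthly behavioral health and pediatric department meetings". It lists AIM, FIM and IAM, and its analytic methods are "Descriptive statistics. Repeated measures ANOVA". Of these, "Repeated measures ANOVA" is the only inferential method named in the article, and it serves the aim, given in the abstract's Methods, of following provider perceptions over time.

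Three other statements bear on how complete the ratings can be:

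- Educating Providers on Project YES: "Monthly check-ins at department meetings will be held to review processes, answer questions, and gather assessments as well as informal feedback". No other route for collecting the ratings is described.
- The same section says that site meetings let the behavioral health lead "introduce new clinical team members to the intervention and referral processes during their orientation", so some staff are expected to arrive after launch.
- Results: "The program will continue for 6 months before the program evaluation will commence". The start was staggered: one site in November 2022, then "expanded across all sites in December 2022".

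The Setting section gives 13 providers on the pediatric behavioral health team. Pediatric medical providers are also in scope, but their number is not given. Nor does the article say whether ratings are linked by provider from month to month.

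**The concern.** Standard repeated measures ANOVA needs a full set of ratings from each provider; a provider with one gap contributes nothing. Here the ratings come from attendance at a recurring meeting, where gaps are to be expected. A provider who joins after the first rating cannot have a full set, whatever their later attendance.

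At stake is the only planned test of whether acceptability, feasibility and appropriateness change during the pilot. A test run on a reduced group loses precision. If those who attend every meeting also rate differently, it describes an unrepresentative group as well. The staggered start adds a smaller point: at the first site, a given calendar month stands for one more month of experience than elsewhere.

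**Working it through.** The article gives no sample size, attendance or missing-data figure for this analysis, so there is no stated figure to reproduce. The check asks how many providers would have complete sets over a plausible range.

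**Inputs**

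- Number of waves, k: about 6, from monthly collection over 6 months. The exact count is not stated; 3 to 7 is taken as the range.
- Attendance, p: not stated. Assumed values of 70% to 95%.
- Behavioral health team: 13 (Setting).

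**Step 1. Independent absences.** The complete share is p^k. For k = 6:

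| Attendance | Complete share | Of 13 providers |
|---|---|---|
| 70% | 0.70^6 = 12% | 1.5 |
| 80% | 0.80^6 = 26% | 3.4 |
| 90% | 0.90^6 = 53% | 6.9 |
| 95% | 0.95^6 = 74% | 9.6 |

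**Step 2. Attendance at which half are lost.** Solve p^k = 0.5, so p = 0.5^(1/k). This gives 0.794 for 3 waves, 0.841 for 4, 0.871 for 5, 0.891 for 6 and 0.906 for 7.

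**Step 3. Clustered absences.** Let attendance vary between providers as a beta distribution with mean m and intraclass correlation ρ. Put s = 1/ρ − 1 and a = m·s. The complete share is the product of (a + j)/(s + j) for j = 0 to k − 1. With m = 0.80, ρ = 0.5 and k = 6, s = 1 and a = 0.8, so

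0.8/1 × 1.8/2 × 2.8/3 × 3.8/4 × 4.8/5 × 5.8/6 = 0.59.

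At 80% attendance the share is 35% for ρ = 0.1, 49% for ρ = 0.3 and 59% for ρ = 0.5. At 90% it is 61%, 71% and 78%.

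**Step 4. Selection.** With p = 0.80, ρ = 0.3 and 6 meetings, let r be the correlation between a provider's rating and their propensity to attend. In simulation, complete cases rate 0.00 SD too high at r = 0, 0.22 SD at r = 0.3 and 0.36 SD at r = 0.5. This is bias in the mean level, not in the change.

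**Step 5. Effect on the estimated change.** A separate simulation assumed 60 providers, 79% attendance and attendance depending on the previous rating (200 replicates, 27% complete). The true change was −0.41. Complete cases gave −0.36 (SD 0.18) and a mixed model −0.37 (SD 0.09). The bias is nearly the same; the SD is halved. The strength of the assumed dependence is not recorded, so this is illustration only.

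**Step 6. After the change.** A mixed model uses every provider with at least one rating. At 80% independent attendance over 6 meetings that is 1 − 0.2^6, or more than 99.9%, against 26% as complete cases.

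**The case against.** The strongest reply is that a method label in a condensed article on a quality improvement pilot is not a commitment to discard incomplete providers, and that missing-data handling is usually left to the analysis plan. The second half stands: silence about absentees is not a fault here. The first half stands only in part. The article does name the method, and its ordinary meaning is the complete-set analysis. If a mixed model was intended, naming it costs nothing.

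A reader might infer more than the documents support:

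- **That most of the data are discarded.** No attendance figure is given. Half or more are kept at attendance above about 89% with independent absences, or at 80% with strong clustering.
- **That the sample is small.** This is documented only for the 13 behavioral health providers.
- **That the analysis favours engaged or favourable providers.** Nothing links attendance to ratings. Absence for leave or clinic schedules would cause no bias.
- **That the provider outcomes as a whole rest on a selected remnant.** The descriptive statistics can use every rating. They do not replace the test, however, because monthly means can move simply because the raters change.

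Two further points stand. The staggered start is a one-month offset at one site, and the article gives no number for later joiners, nor does it say that they enter the rating panel. That the programme's own lead runs the check-ins is a separate response-bias question, which a change of model would not answer.

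**Conclusion.** The point holds in a limited form and is worth correcting. The named method does not suit ratings gathered through meeting attendance, because it drops any provider with one gap, including anyone who joins the panel after the first rating.

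The size depends on unstated attendance. Over the range checked for 6 meetings (70% to 95% attendance, independent absences), between 12% and 74% of providers would be complete. The harm falls on the test of change over time, and mainly on its precision. Bias from selection is possible but conditional on attendance being related to the ratings. The loss of providers does not depend on that condition, and it is enough to justify the change.

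**What to change.** In the provider row of Table 1, replace repeated measures ANOVA with a linear mixed model for each of AIM, FIM and IAM. Use all available ratings, with a random intercept for provider and fixed effects for time (months since site launch) and department. Keep the descriptive statistics, and report the number of raters and the response rate beside each monthly mean.

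The cost is one changed table entry and a count of raters each month. Ratings must be linked by a coded provider ID, but the ANOVA needs that too. The model assumes that missingness is explained by the observed ratings; if providers stay away for reasons tied to ratings they never gave, some bias remains. The monthly response rates let readers judge how much rests on that assumption.

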### Provider Measures

A total of 3 implementation outcome measures will be collected from providers to evaluate the implementation of Project YES. Each outcome measure consists of 4 items rated on a 5-point Likert scale ranging from “completely disagree” to “completely agree.” The scales demonstrate high reliability, with Cronbach α reported between .85 and .91, structural validity indicated by factor loadings between 0.75 and 0.89, and test-retest reliability coefficients between 0.73 and 0.88 [29].

#### Acceptability of Intervention Measure

The Acceptability of Intervention Measure (AIM) measures the appeal of an intervention to target providers (eg, Project YES meets my approval) [29].

#### Intervention Appropriateness Measure

The Intervention Appropriateness Measure (IAM) measures whether an intervention is fitting and relevant to the target participants within a given setting (eg, Project YES seems applicable) [29].

#### Feasibility of Implementation Measure

The Feasibility of Intervention Measure (FIM) measures whether implementing a given intervention is achievable within the setting given the time and resources required to carry it out successfully (eg, Project YES seems doable) [29].

### Participant Measures

The following measures are the same as those described in previous reports on Project YES; however, in the context of this data collection, we include both the English and Spanish versions. Additionally, this study implemented a single-item question in both English and Spanish surveys, asking whether the participant was a patient with RMG. Only data from participants who select yes to confirm patient status with RMG and report being between the ages of 13 and 17 years will be included in the final analysis.

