**Objective:**

We aimed to implement a clinical workflow for primary care and behavioral health providers to refer patients aged 13 to 17 years with mild to moderate depression and anxiety symptoms to Project YES (Youth Empowerment and Support), an open-access SSI platform, in a large group medical practice with an integrated behavioral health department.

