Web-based SSIs have been evaluated in a more naturalistic setting through an open-access web-based platform called Project YES [19]. Project YES allows adolescents (aged 11 to 17 years) to choose from 3 web-based interventions, each of which spans approximately 30 minutes and includes a core element of evidence-based treatment [10]. Youth may choose from Project Personality (which teaches that personality traits can change), Project CARE (which centers on the benefits of self-compassion), or the Action Brings Change (ABC) project (which encourages youth to engage in activities to improve their mood). Youth can complete as many interventions as they would like, as often as they choose to, and entirely free of charge. In a pilot trial, adolescents who completed an intervention through the Project YES platform experienced immediate improvements in hopelessness, self-hatred, perceived control, and agency. In addition, youth rated the interventions as acceptable, and 34.32% of youth who started an intervention completed it [10]. This surpassed completion rates for other digital interventions in naturalistic settings (1%-28%) [20].

Project YES has also been culturally adapted and translated into Spanish for youth living in San Antonio, Texas. Through a series of semistructured focus groups, San Antonio youth stakeholders shared their lived mental health experiences and co-designed the adapted interventions [21]. San Antonio youth who completed an intervention in English experienced immediate improvements in hopelessness, self-hatred, and perceived agency. Similarly, youth who completed a culturally adapted and translated intervention experienced immediate improvements in self-hatred [21]. The completion rate was 49.6%, and the interventions were rated as acceptable by youth [21].

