#### Demographics

Participants will identify their age range (provided in ranges to maintain anonymity: 10 years or younger, 11-12 years, 13-15 years, 16-17 years, 18 years or older), sex assigned at birth, gender identity, sexual orientation, race or ethnicity, how they learned about Project YES, and whether they are patients at RMG in Massachusetts.

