### Strengths and Limitations

Offering patients SSIs in primary care and behavioral health settings is an efficient and cost-effective approach to narrowing the treatment-to-service gap in adolescent mental health care. Approaching this as an implementation project will allow us to understand the feasibility, acceptability, and appropriateness of SSI delivery in a pediatric primary care and integrated behavioral health setting and thus identify potential barriers and facilitators providers may face when offering Project YES to their patients. This information may be used to iteratively adapt the clinical workflow described to streamline the process for providers and patients alike, thus improving uptake. This protocol was developed in close collaboration with a pediatric clinical team and feedback from leadership to ensure that it is relevant, efficient, and can be easily grasped and deployed by providers. Further, making the SSIs accessible to patients with a wide range of symptoms may help reduce stigma around mental health care. Finally, adolescents who may otherwise forgo behavioral health services due to concerns about their confidentiality from their parents can use the SSIs privately without their parents being notified.

Nonetheless, there are several limitations to the study design. Participation is contingent on elevated scores on the screener questionnaires. However, patients who may not meet clinical criteria may also benefit from the SSIs, which can be effective for subclinical internalizing symptoms. To address this, future iterations of this project may explore expanding referrals to all adolescent patients, regardless of meeting screening criteria, or advertising the program on waiting room monitors and in other patient-facing materials. Additionally, this work is only being piloted at a single-group medical practice in Massachusetts and may not be generalizable to other populations. Furthermore, RMG has a predominantly White, English-speaking patient population. Although the intervention is available to Spanish-speaking patients, more work may be needed to understand its feasibility and acceptability in other clinical contexts and among diverse patient populations. Finally, without the use of a placebo-control group to control for potential effects of participating in an SSI in and of itself, the effectiveness data from this study may overestimate potential improvements in symptoms.

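### The patient analysis set rests on self-declared practice membership and age, not on referral or screening, and its counts of patients cannot be told apart from counts of sessions

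*Protocol article*

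**What the plan says.** - **Who is analysed.** Participant Measures states the rule for the final analysis: "Only data from participants who select yes to confirm patient status with RMG and report being between the ages of 13 and 17 years". Patient Participation gives the mechanism: "By entering that they are an RMG patient, the Lab for Scalable Mental Health will be able to filter RMG’s data for the program evaluation". No other condition is named.
- **Who can reach the site.** The Objective calls Project YES "an open-access SSI platform".
- **What identifies a record.** Patient Participation: "The patient will not enter any potentially identifying information". The questionnaires before and after the module are anonymous and optional.
- **Repeat use.** Evidence for SSIs: "Youth can complete as many interventions as they would like, as often as they choose to". Three modules are on offer.
- **What is counted.** Data Collection takes referrals from the electronic health record and engagement from the anonymous site data. Table 1 lists, as patient metrics, the practice's patients who entered the site and "Total number of patients who completed the SSI", plus the Program Feedback Scale, all summarised descriptively.
- **A source item.** Demographics includes "how they learned about Project YES". It plays no part in the inclusion rule.
- **Target population.** The last paragraph of Evidence for SSIs sets the primary objective as feasibility and acceptability of delivery to adolescents with mild to moderate depression and anxiety in primary care and behavioral health.

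**The concern.** The population in the objective and the population in the patient analysis are defined by different rules. The first is reached through screening and a provider's referral. The second is whoever ticks two boxes on a public site. An adolescent of the practice who was never screened, who fell below the thresholds, who met the exclusion criterion, or who found the site through other channels satisfies the second rule.

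Three things are at stake:

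- The Program Feedback Scale is the only patient acceptability measure named. It would be summarised in a group that may differ from the target group.
- If entrants are set against referrals to describe patient uptake, the two numbers come from unlinked sources and the first need not be part of the second.
- The engagement counts are labelled as patients, but the records as described cannot show whether two sessions came from one person or two.

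The Results section says that referral and engagement data will be reviewed iteratively to adapt the workflow, so a misreading could influence the rollout while it is running.

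**Working it through.** The protocol states no target or expected value for patient uptake or completion in this study, so there is no figure to reproduce. The check has two parts.

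**1. The rules side by side**

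| Step | Condition stated | Source |
|---|---|---|
| Referral | Age 13 to 17, at least one elevated screener, language, no active suicidal ideation | Inclusion and exclusion box |
| Count of referrals | Provider action in the record system | Data Collection, Table 1 |
| Patient analysis set | Self-declared practice patient, self-reported age 13 to 17 | Participant Measures |
| Link between the last two rows | None described; no identifying information entered | Patient Participation, Data Collection |

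The third row does not imply the first. It can also miss referred patients: someone who leaves before answering the practice item, or does not tick it, cannot be recognised as a patient of the practice, because that item is the only marker described.

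**2. How far the figures could move (illustration)**

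Every input in this part is an assumption, except the two completion rates, which Evidence for SSIs reports from earlier Project YES work.

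*Entry.* Let 200 patients be referred and 80 truly enter, so the true rate is 80/200 = 40%. Let d be the share of referred entrants not recorded as practice patients, n the non-referred share of recorded users, and m the sessions per user. Then

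apparent rate = true rate × (1 − d) / (1 − n) × m.

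| d | n | m | Apparent rate |
|---|---|---|---|
| 0 | 0 | 1.0 | 40% |
| 0.2 | 0 | 1.0 | 0.40 × 0.8 = 32% |
| 0.2 | 0.2 | 1.0 | 0.40 × 0.8 / 0.8 = 40% |
| 0 | 0.1 | 1.25 | 0.40 / 0.9 × 1.25 = 55.6% |
| 0.2 | 0.2 | 1.5 | 0.40 × 0.8 / 0.8 × 1.5 = 60% |
| 0 | 0.2 | 1.5 | 0.40 / 0.8 × 1.5 = 75% |

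The errors can lower the figure, raise it, or cancel.

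*Completion.* Take 80 persons and 20 further sessions that cannot be linked to them. If none of the extra sessions is completed, the session-level rate is 80c/100. If all are completed, by persons who had already completed once, it is (80c + 20)/100.

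- c = 34.32%: 80c = 27.456, so the rate runs from 27.5% to 47.5%.
- c = 49.6%: 80c = 39.68, so the rate runs from 39.7% to 59.7%.

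With no repeat sessions, completion does not change.

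**The case against.** The strongest reply is that this is a descriptive quality improvement pilot. Its Abstract names provider uptake and provider-rated acceptability, feasibility and appropriateness as what will be examined. Those come from the record system and from provider questionnaires, and nothing here touches them. Table 1 lists patient counts, not a ratio of entrants to referrals or a completion rate. The item on how participants heard of the platform would allow some separation of sources, and a rule for removing duplicates may sit in a fuller plan. Anonymity is deliberate, given the confidentiality concerns in the Introduction.

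Most of this stands and limits the point. It does not remove it: the inclusion rule is stated outright rather than left open, it omits referral and eligibility, and it governs the only named patient acceptability measure.

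Some stronger readings are tempting but not supported:

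- *Repeats are counted as new patients.* No section says so. Repeats are allowed, no identifier exists, and no counting rule is given. That makes persons and sessions indistinguishable as described, and no more.
- *Uptake or completion is inflated by a given amount.* Early exits and an unticked practice item pull apparent entry down, while repeats and non-referred users push it up. The documents fix neither size nor direction.
- *The count of QR code against MyChart access is wrong.* It sits in the provider row of Table 1 and records the option selected at the visit. The plan does not claim that it shows the route later used.
- *Strengths and Limitations contradicts the inclusion rule.* The sentence "Participation is contingent on elevated scores on the screener questionnaires" reads naturally as describing the referral workflow, not the analysis set. It would mislead only if applied to the analysed site data.

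**Conclusion.** The point holds in a limited form and is of moderate importance. The patient analysis set is not restricted or linked to referred, screen-eligible adolescents, so patient acceptability and engagement need not describe the population in the primary objective. A ratio of entrants to referrals formed from these data would not be a proper proportion. The Table 1 engagement counts cannot, as described, be read as counts of persons.

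The size is unknown. The ranges of 32% to 75% around a true 40% entry rate, and about 27% to 48% around a 34.32% completion rate, show only that modest assumed departures could matter. The conclusion itself needs only the stated inclusion rule, open access, anonymity and unlimited repeat use. It would lapse if the full protocol ties the site data to referral and states a rule for repeat sessions.

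**What to change.** 1. **Define the main patient set by referral.** Add a non-identifying tag for the practice's referrals to the MyChart link and to the QR codes, and make tagged arrivals the main set. Alternatively, stratify the self-declared set by the existing item on how participants heard of Project YES, and report those with a missing answer as a separate group.
2. **Keep the self-declared set as a sensitivity analysis.**
3. **Label the Table 1 engagement counts as sessions**, unless first use is identified, for example by one item asking whether this is the participant's first time.
4. **Do not present untagged site counts as a proportion of referred patients.**

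The cost is a link parameter, at most one extra item, and wording changes in Patient Participation, Data Collection and Participant Measures. No identifier is needed, so anonymity is kept.

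There are drawbacks. Forwarded links and skipped optional items leave some misclassification, and restricting to those who name a provider would lose referred users who skip the item. The reported patient counts may be smaller. Because the program began in November 2022, a tag helps only arrivals after it is added; for earlier records, stratification by the existing item is the available route.
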